**Methods:**

This study will adopt a convergent mixed-methods design comprising three primary phases: (1) Quantitative phase: a cross-sectional survey will be conducted among older adults diagnosed with osteoporosis. Data collection will include demographic variables, scores from the Edmonton Frail Scale, Activities of Daily Living assessments, Nutritional Risk Screening assessments, and the Hospital Anxiety and Depression Scale. In addition, handgrip strength will be measured, alongside relevant laboratory parameters. Data will undergo descriptive analysis, followed by univariate analyses and multivariate binary logistic regression to identify factors associated with frailty. (2) Qualitative phase: semi-structured, face-to-face interviews will be performed with participants classified as frail according to their frailty assessment scores, enabling an in-depth exploration of their subjective perceptions and experiences of frailty within the context of osteoporosis. (3) Integration phase: key findings from both quantitative and qualitative components will be analyzed and synthesized to generate a comprehensive understanding of the phenomenon.

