Frailty is an age-associated geriatric syndrome that represents a critical intermediate state in the aging trajectory. Its defining feature is a decline in physiological reserve, resulting in markedly reduced resilience to both endogenous and exogenous stressors (8). This decline is underpinned by measurable biological processes across multiple domains. Consensus biomarkers for frailty highlight systemic involvement, specifically encompassing the physiological domain (e.g., insulin-like growth factor 1), the inflammatory domain (e.g., high sensitivity C-reactive protein, interleukin-6), and the epigenetic domain (e.g., DNA methylation/epigenetic clocks) (9). Furthermore, frailty extends beyond these physiological deficits to a multidimensional syndrome that severely compromises functional independence (as measured by muscle mass and handgrip strength) and encompasses psychosocial domains, including social support and psychological well-being (10). The clinical significance of this complex syndrome is evidenced by its high prevalence, with epidemiological studies reporting rates reaching 29.8% in hospital settings, and pre-frailty observed in an additional 39.3% of patients (11).

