This study aims to: (1) determine the prevalence and current status of frailty among older adults with osteoporosis; (2) identify factors associated with frailty within this population; (3) explore the subjective illness experiences of frailty in older adults with osteoporosis; (4) analyse potential discrepancies between healthcare system frailty management recommendations and patients' illness perceptions; and (5) elucidate conflicting mechanisms between qualitative and quantitative findings through triangulation analysis. By addressing these objectives, this research seeks to provide evidence-based insights to inform the development of precise, patient-centered nursing care and health policy.

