**Figure 1 F1:**
[figure not shown]
Flowchart of the convergent mixed-methods study design.

The study will proceed through three sequential yet interrelated phases:

(1) Quantitative phase

A cross-sectional survey will be administered to older adults diagnosed with osteoporosis.Data will include: demographic characteristics; Edmonton Frail Scale (EFS) scores; Activities of Daily Living (ADL) assessments; Nutritional Risk Screening (NRS) scores; Hospital Anxiety and Depression Scale (HADS) scores; handgrip strength measurements; and relevant laboratory parameters.Statistical analysis will involve descriptive statistics, univariate analyses, and multivariate binary logistic regression to identify factors associated with frailty.

(2) Qualitative phase

Semi-structured, face-to-face interviews will be conducted with patients classified as frail based on their frailty scores.This component aims to provide an in-depth exploration of participants' lived experiences of frailty in the context of osteoporosis.

(3) Integration phase

Principal findings from both datasets will be compared and synthesized.Integration will be achieved through joint display analysis and narrative synthesis, enabling the identification of convergent, complementary, or divergent findings.his phase is designed to yield novel insights and enhance clinical practice guidance for frailty management in osteoporotic patients.

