#### Instrument

Data will be collected using the following research instruments:

The General Information Questionnaire will collect 17 variables: sex, age, height, weight, body mass index (BMI), marital status, living arrangements, educational attainment, monthly household income, medical expense reimbursement method, presence of insomnia, exercise habits, smoking status, alcohol consumption, calcium supplementation, history of falls within the previous 6 months, and 17 comorbid conditions.Edmonton Frail Scale (EFS): developed by Rolfson et al. in 2006, the Edmonton Frail Scale (EFS) provides a comprehensive assessment of frailty encompassing physical, psychological, and social domains (22). This 11-item instrument evaluates frailty across nine key domains: cognition, general health status, independence, social support, medication use, nutrition, mood, continence, and self-reported functional performance. Cognitive function is assessed using the Clock Drawing Test, while mobility is measured via the Timed Up and Go (TUG) test. Independence in activities of daily living is quantified by the number of independently completed tasks out of eight routine activities, including cooking, cleaning, and shopping. The EFS yields a total score ranging from 0 to 17, with higher scores indicating greater frailty severity. The scale is user-friendly, practical, and can be administered within approximately 10 min, making it suitable for rapid frailty screening by both healthcare professionals and trained non-professionals. Internal consistency is acceptable, with a reported Cronbach's alpha coefficient of 0.62.Activities of Daily Living Assessment Scale (ADL): the Barthel Index is a widely used instrument to evaluate activities of daily living in older adult patients. This scale comprises 10 items, including feeding, grooming, dressing, bowel control, bladder control, toilet use, transfers (bed to chair), ambulation on level surfaces, and stair climbing (23). The total score ranges from 0 to 100, with higher scores indicating greater independence in performing daily self-care tasks. Based on the total score, patients' functional status is classified into five categories: complete dependence (0–20 points), severe dependence (21–40 points), moderate dependence (41–60 points), mild dependence (61–99 points), and complete independence (100 points).Nutritional Risk Screening Assessment Scale: the Nutritional Risk Screening 2002 (NRS-2002) was developed through international collaboration among researchers from Denmark, the United Kingdom, France, and other countries. It is designed to evaluate changes in nutritional status based on parameters such as weight variation over the preceding 3 months and dietary intake during the past week (24). The scale demonstrates moderate reliability, with a Kappa coefficient (κ) of 0.67, a sensitivity of 0.86, and a specificity of 0.37.Hospital Anxiety and Depression Scale (HADS): developed by Zigmond et al. in 1983, the Hospital Anxiety and Depression Scale (HADS) is a self-administered instrument designed to evaluate anxiety and depression symptoms experienced by patients over the preceding week (25). It comprises two subscales—anxiety and depression—each containing seven items scored on a four-point Likert scale ranging from 0 to 3. The total score for each subscale ranges from 0 to 21. Scores are interpreted as follows: 0–7 denotes no clinically significant symptoms; 8–10 indicates possible presence of anxiety or depressive symptoms; and 11–21 reflects probable clinical anxiety or depression. The internal consistency reliability, expressed by Cronbach's α coefficients, is 0.879 for the total scale, and 0.806 for both the anxiety and depression subscales.Muscle Strength Assessment: muscle strength will be evaluated using a handheld dynamometer. Participants will be instructed to perform a maximal voluntary isometric contraction by gripping the dynamometer handle with their dominant hand for 2–3 s. Two measurements will be recorded, with the highest value (expressed in kilograms) retained as the final result, reported to two decimal places.Laboratory Indicators: within 24 h of admission, the following laboratory parameters will be collected: neutrophil percentage (%), hemoglobin (g/L), C-reactive protein (mg/L), serum calcium (mmol/L), and serum creatinine (μmol/L). Normal reference ranges are as follows: neutrophil percentage: 40–75%. Hemoglobin: 130–175 g/L for males, 115–150 g/L for females. C-reactive protein: 0–10 mg/L. Serum calcium: 2.11–2.52 mmol/L. Serum creatinine: 57–111 μmol/L for males, 41–81 μmol/L for females.

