#### Participants

Following purposive sampling principles, a representative sample will be selected based on factors including age, educational attainment, and frailty severity (26). Participants identified as frail according to the Edmonton Frail Scale will be recruited for semi-structured, face-to-face interviews. All participants will provide informed consent and voluntarily agree to participate in the study.

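### The graded 0-17 Edmonton Frail Scale enters the factor analysis only as frail/not frail; adding an analysis of the full score would recover about 25 to 30% of the outcome information for one extra model

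*Protocol article*

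**What the plan says.** All references are to the protocol article.

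- **The scale.** Stage 1, Instrument: "The EFS yields a total score ranging from 0 to 17, with higher scores indicating greater frailty severity". No score is given at which a participant counts as frail, and no intermediate or severity bands are given. The same section prints five bands for the Barthel Index and three for each HADS subscale.
- **Prevalence.** The first aim, in the Introduction, is to "determine the prevalence and current status of frailty among older adults with osteoporosis".
- **Factors.** The Abstract plans "multivariate binary logistic regression to identify factors associated with frailty", and Study design repeats the binary model. No other regression of the EFS is described.
- **Interviews.** Study design: "Semi-structured, face-to-face interviews will be conducted with patients classified as frail based on their frailty scores". Stage 2, Participants, names the instrument: "Participants identified as frail according to the Edmonton Frail Scale will be recruited for semi-structured, face-to-face interviews". That section also lists frailty severity among the features on which the purposive sample is chosen.
- **Intermediate state.** The Introduction treats pre-frailty as a state of its own, citing "rates reaching 29.8% in hospital settings, and pre-frailty observed in an additional 39.3% of patients".

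**The concern.** One two-way split serves the prevalence estimate, the regression outcome and interview eligibility. In the regression, a participant just above the cut is treated like one at the top of the scale, and one just below it like one at the bottom. The severity information is collected and then not used to identify associated factors, which is the second aim.

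At stake is mainly power for binary candidate factors. Stage 1, Instrument, lists many that are binary or easily become so: sex, smoking, alcohol, insomnia, calcium supplementation, recent falls and 17 comorbid conditions. A secondary matter is that a single frail percentage does not show how many participants lie in the intermediate range that the article itself recognises.

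**Working it through.** **1. The plan's own figures.** Stage 1, Sample size, gives P = 0.533, d = 0.0533 and z = 1.96.

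- Prevalence: 1.96² × 0.533 × 0.467 / 0.0533² = 336.6, so 337. The article states 343, a difference of under 2%.
- Non-response: 343 × 1.1 = 377.3, so 378, as stated. If 10% of 378 do not respond, 378 × 0.9 = 340 remain. I use 340 below.
- Regression: OR 1.6, two-sided 0.05, power 0.80. For a continuous factor per standard deviation (SD), N = (1.96 + 0.842)² / [p(1−p) × (ln 1.6)²]. With p = 0.533 this is 7.85 / (0.2489 × 0.2209) = 143, which agrees with the article's statement that fewer than 343 are needed. The article does not say which type of factor it assumed.

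**2. Inputs for the comparison.**

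- Frail proportions for osteoporosis in the article: 53.3% (Sample size) and 37.8% (Introduction).
- OR 1.6 and two-sided 0.05, from Sample size.
- Assumptions of mine, not in the documents: proportional odds, so that the same OR applies at every cut; an EFS that is roughly bell-shaped with mean 7 and SD 3; no adjustment for other covariates.

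**3. Outcome information per participant.**

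- Split: p(1−p), which is 0.2489 at 53.3% and 0.2351 at 37.8%.
- Full score: (1 − Σpᵢ³)/3. Under the assumed distribution Σpᵢ³ is about 0.010, giving 0.330. The ceiling is 1/3, so the result depends little on the assumed mean and SD.
- Ratios: 0.330/0.2489 = 1.33 and 0.330/0.2351 = 1.40.
- Loss against the ceiling: 1 − 3p(1−p) = 25% and 30%. Against 0.330 it is 25% and 29%.

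**4. Power.** Power = Φ(ln 1.6 × √(N × v × info) − 1.96), with N = 340. For a binary factor with exposure e, v = e(1−e). For a continuous factor per SD, v = 1.

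| Factor | Split, 53.3% frail | Split, 37.8% frail | Full score |
|---|---|---|---|
| Binary, 50/50 | 58% | 56% | 70% |
| Binary, 20% exposed | 41% | 39% | 51% |
| Continuous, per SD | 99% | 99% | >99% |

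Example, 50/50 factor at 53.3% frail: 0.470 × √(340 × 0.25 × 0.2489) − 1.96 = 2.162 − 1.96 = 0.202, and Φ(0.202) = 0.58. With the full score: 0.470 × √(340 × 0.25 × 0.330) − 1.96 = 0.529, and Φ(0.529) = 0.70.

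**5. How much of the shortfall is due to the split.** For 80% power with a 50/50 factor, N = 7.85 / (0.2209 × 0.25 × info). This is 571 with the split at 53.3% frail, 604 at 37.8%, and 431 with the full score. All exceed 340, so the full score narrows the gap without closing it.

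**6. Sensitivity to the model.** If the score is treated as normal instead of under proportional odds, the loss is 1 − φ(z_p)²/[p(1−p)], which is 37% at 53.3% frail and 39% at 37.8%. The 25 to 30% is therefore the lower of the two results.

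**The case against.** The strongest reply is that the binary model suits the purpose. Prevalence needs a frail/not frail rule, the sample size rests on that proportion, and clinicians act on the classification. This stands: a binary outcome is a legitimate choice. An ordinal model on up to 18 levels also adds a proportional-odds assumption and may meet sparse upper scores, so whether it should be the main analysis is a matter of judgement.

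It also stands that many candidate factors are continuous or scored (age, BMI, grip strength, laboratory values, HADS), and for these the split costs almost nothing. For binary factors, sample size is the larger problem.

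The missing cut, taken alone, is detail that a condensed article may leave to the scale's cited source. The NRS-2002 description gives no threshold either.

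Three stronger readings are tempting, but the documents do not support them:

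- **A 39-point swing in prevalence.** The Introduction's figures give 29.8% or 29.8 + 39.3 = 69.1%, depending on where the pre-frail are counted. They describe hospital settings in general, with no instrument named, and the sum moves the whole class across the cut. It is at most an illustration, not a forecast for this sample.
- **Misclassification inferred from alpha.** The article reports: "Internal consistency is acceptable, with a reported Cronbach's alpha coefficient of 0.62". Alpha measures internal consistency across items. It gives no misclassification rate at a cut, and nothing in the article shows the direction of any resulting bias.
- **A cut chosen after seeing the scores.** Interviewees are to be selected as frail while the survey is under way, so some working cut must already be in use. Nothing points to a later choice.

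**Conclusion.** The point holds as a worthwhile improvement, not as an error in the binary model. The only regression of the EFS that the article describes discards about 25% of the outcome information at 53.3% frail and about 30% at 37.8%. For a 50/50 binary factor with OR 1.6 and 340 respondents, that means power of about 58% and 56% instead of about 70%. Factors measured on a continuous scale remain at about 99% per SD.

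These sizes rest on proportional odds, an assumed bell-shaped score and unadjusted power. The article gives no EFS distribution. The order of magnitude does not hinge on the assumed mean and SD, but it does depend on the model, and a normal score would put the loss higher.

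**What to change.** - Keep the binary logistic model as the clinical contrast. Add a pre-specified ordinal (proportional-odds) or continuous-score regression of the EFS total with the same candidate factors. If it is ordinal, state how proportional odds will be checked and that upper scores will be pooled if sparse.
- State the EFS cut and its source before scores are analysed, and use that one cut for prevalence, regression and interview eligibility.
- Report the not frail, intermediate and frail proportions, each with a confidence interval, and use the same classes where interview sampling refers to severity.

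Cost: a few sentences, one model and one table, on data already being collected. The downside is small: one added modelling assumption, and odds ratios per shift in score that are less familiar to clinicians. The retained binary model covers the latter.

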## Materials and methods

### Study design

This study will employ a convergent mixed-methods approach, involving the concurrent collection of quantitative and qualitative data within the orthopedic wards of a tertiary hospital from February to December 2025. Data will be analyzed separately before integrating the results (see Figure 1).

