#### Participants

Inclusion criteria are:

(1) Age ≥ 65 years;(2) Osteoporosis Diagnosis: diagnosis of osteoporosis based on any of the following:

a dual-energy *X*-ray absorptiometry (DXA) *T*-score of ≤ −2.5 at the axial skeleton or distal one-third radius;a history of fragility fracture of the hip or vertebra;osteopenia (−2.5 < *T*-score < −1.0) accompanied by a fragility fracture of the proximal humerus, pelvis, or distal forearm (20);

(3) Possessing good communication skills, the ability to read questionnaires effectively, and intact cognitive function (e.g., scoring ≥24 on the Mini-Mental State Examination [MMSE] threshold);(4) voluntary participation with signed informed consent.

Exclusion criteria are:

(1) Patients with other critical or unstable illnesses, such as active malignant tumors or severe, acute cardiorespiratory insufficiency;(2) Patients exhibiting severe disability, bedridden status, or conditions that severely limit mobility required for frailty assessments;(3) A history of stroke or severe head trauma, or existing central nervous system diseases;(4) Individuals unable to cooperate with questionnaire surveys or frailty assessments.

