
#### Date collection

Under the supervision of the research team, standardized training on study procedures will be provided. After explaining the study's purpose and significance and obtaining informed consent, data will be collected via one-to-one interviews. For inpatients, questionnaires will be administered following their daily treatments and once they report no significant discomfort. If participants are unable to complete the questionnaire independently, the investigator will record responses based on participants' verbal reports.

Demographic data, Edmonton Frail Scale (EFS) scores, Activities of Daily Living (ADL) assessments, Nutritional Risk Screening (NRS) assessments, Hospital Anxiety and Depression Scale (HADS) scores, and muscle strength measurements will be collected through face-to-face interviews. Laboratory parameters will be retrieved from the electronic medical records system. Each questionnaire is estimated to require 15–20 min for completion. All questionnaires will be administered and collected on-site.

Following the survey, investigators will offer psychological support to participants to mitigate any distress experienced during questionnaire completion. Throughout the study, the ethical principles of autonomy, confidentiality, and non-maleficence will be rigorously upheld. Finally, all assessment results will be independently reviewed by two qualified medical professionals with a minimum of intermediate-level clinical credentials to reduce potential bias.

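### Grip is tied to the dominant hand although arm fractures are eligible, and no listed variable captures acute fracture, surgery or assessment date, so acute injury can be read as frailty biology

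*Protocol article*

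**What the plan says.** The Instrument section under Stage 1 measures maximal grip by "gripping the dynamometer handle with their dominant hand" and keeps the better of two attempts. It gives no alternative for an injured arm.

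The Participants section accepts several routes to the diagnosis. One is a qualifying T-score alone. Another is "a history of fragility fracture of the hip or vertebra". A third is osteopenia "accompanied by a fragility fracture of the proximal humerus, pelvis, or distal forearm". None of the fracture routes limits recency, and the arm-fracture route does not limit side.

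Study design places data collection "within the orthopedic wards of a tertiary hospital". For the bloods, Instrument says that "within 24 h of admission, the following laboratory parameters will be collected"; these include CRP, neutrophil percentage and haemoglobin. For the questionnaires, the Date collection section says: "For inpatients, questionnaires will be administered following their daily treatments and once they report no significant discomfort". No day relative to admission, injury or surgery is given.

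Instrument itemises 17 general variables. The nearest to injury are falls in the past 6 months and a set of 17 unnamed comorbidities. Fracture site, side or date, surgery, and date of assessment are not among them. Under Data analysis, the logistic model takes variables with univariate p < 0.05 plus covariates chosen with clinical experts.

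**The concern.** There are two linked problems.

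**Grip.** The eligibility rule admits patients for whom the grip procedure may not measure strength. A recently broken dominant wrist or shoulder lowers grip, or prevents the test, for a reason that has nothing to do with frailty.

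**Confounding.** On an orthopaedic ward, a recent injury can raise CRP and neutrophils and lower haemoglobin and grip. It can also worsen the Timed Up and Go and the independence items that feed the EFS. It may therefore drive both the candidate predictors and the outcome.

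The second aim of the study is to identify factors associated with frailty. The Introduction already presents high-sensitivity CRP as a frailty biomarker and grip as a measure of the function that frailty compromises. An association produced by injury would look like confirmation of that picture. If injury status is not recorded in the study data, the analysis cannot separate the two explanations.

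**Working it through.** **The plan's own figure.** With P = 0.533 and d = 0.0533, n = 1.96² × 0.533 × 0.467 / 0.0533² = 336.6, so 337 against the stated 343. Rounding to P = 0.53 and d = 0.053 gives 341. Inflation: 343 × 1.10 = 377.3, so 378 as stated. The difference is small and nothing below depends on it; I use n = 343 and prevalence 0.533.

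**Grip.** The documents do not give the share of patients with a recent dominant-arm fracture. If it were 5–10%, and those patients were enrolled and tested, the number affected would be 0.05 × 343 = 17 to 0.10 × 378 = 38.

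**Markers.** Assumptions: a share q of patients is acutely injured; injury multiplies the odds of an EFS-frail result by OR; injury shifts the marker by s SD; given injury status, the marker has no link to frailty. Expected group sizes are 343 × 0.533 ≈ 183 frail and 160 not frail.

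*High case: q = 0.5, OR = 3, s = 1.*
- Frailty risk is 0.400 without injury and 0.666 with it; the mean is 0.533.
- Share injured among the frail: 0.5 × 0.666 / 0.533 = 0.625. Among the non-frail: 0.5 × 0.334 / 0.467 = 0.358.
- Spurious mean difference: 1 × (0.625 − 0.358) = 0.267.
- Within-group SD ≈ √(1 + 0.625 × 0.375) = 1.11. SE = 1.11 × √(1/183 + 1/160) = 0.120.
- z = 0.267 / 0.120 = 2.2, so p < 0.05 in about 61% of samples.

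*Mild case: q = 0.2, OR = 1.5, s = 0.5.*
- Frailty risks are 0.513 and 0.612. Injured shares are 0.2 × 0.612 / 0.533 = 0.230 and 0.2 × 0.388 / 0.467 = 0.166.
- Difference: 0.5 × 0.064 = 0.032. SE ≈ 1.02 × 0.108 = 0.110.
- z = 0.29, so p < 0.05 in about 6% of samples.

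Simulation under the same assumptions agrees. Ranges are the spread between repeated runs:

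| q | OR | s | Spurious OR per SD | p < 0.05, univariate |
|---|---|---|---|---|
| 0.2 | 1.5 | 0.5 | 1.03–1.04 | 6–7% |
| 0.2 | 1.5 | 1 | 1.06 | 8–9% |
| 0.3 | 2 | 1 | 1.14 | 22% |
| 0.3 | 3 | 1 | 1.23–1.24 | 46% |
| 0.5 | 2 | 1 | 1.17 | 27–31% |
| 0.5 | 3 | 1 | 1.27–1.28 | 59–61% |

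The planned analysis is multivariable. With two further markers shifted by the same injury in the model, the two 50% rows fall to about 15–17% and 33–37%, and the mild case stays near 5–7%. With injury itself in the model, the marker's odds ratio returns to 0.99–1.01 and the rejection rate to about 5%.

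**The case against.** The strongest reply has four parts.

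**Acute fracture is assumed.** The hip and vertebral route speaks of a history, the arm route gives no date, and a T-score alone also qualifies. This stands. A healed fracture may leave grip unaffected, and an arm that cannot grip may give a missing value, so a reader who infers a known number of invalid, uniformly low values goes beyond the text.

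**Timing and comfort.** A reader might infer that the EFS is done on a later day than the bloods. The text does not say so; it could fall within the same 24 h. Waiting until patients report no significant discomfort is also a partial safeguard. What remains is that the interval is not fixed and its date is not listed.

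**Exclusions.** Bedridden patients and those whose mobility is severely limited are excluded, as are those who cannot cooperate with questionnaires or frailty assessments. This removes some acutely disabled patients. It does not remove a patient with an injured arm who can complete the EFS, since grip is a separate instrument.

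**A condensed article.** The unnamed comorbidities or the expert-chosen covariates might include fracture, and fracture history must be established for the fracture routes. That is possible but not secured: the variables are itemised and none is a fracture or surgery item. The dominant-hand rule is also a stated rule, not an omission.

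The Discussion limits the cross-sectional results to associations. For that reason, too, it cannot be said that injury will be reported as frailty biology, only that it can be read that way.

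**Conclusion.** The point holds in a limited form. The dominant-hand rule and the eligible upper-limb fractures do not fit together, so a recent injury can distort or remove a grip value. Separately, acute injury is a plausible common cause of the admission markers and of EFS items, and no listed variable secures adjustment for it.

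The direction is clear but the size is not. The share of acute admissions, the effect of injury on the EFS and the marker shift are all my assumptions. The 61% figure is the top of the assumed range for the univariate screen and should not be quoted as the expected error rate. At the mild end the effect is almost nil.

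The prevalence calculation behind the sample size is not affected. What is at risk is the interpretation of grip, CRP, neutrophil percentage and haemoglobin as factors associated with frailty. The change should be made because the information is cheap to record and the adjustment cannot be made without it.

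**What to change.** 1. Reconcile the grip procedure with eligibility: where the dominant arm is recently injured, measure the uninjured hand, and record the side used and the reason.
2. From the electronic record already used for the laboratory values, take fracture status, site, side and date, and surgery with its date. Record the date of the EFS and grip assessment.
3. Enter acute fracture or surgery, and time from admission to assessment, as forced covariates whatever their univariate p-value.
4. Repeat the grip and laboratory analyses without acute-fracture admissions.

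The cost is a few form fields, one line in the grip procedure and 2–3 extra model parameters, which is modest against about 160 patients in the smaller outcome group (343 × 0.467). The repeat analysis will be less precise because it uses fewer patients. The Introduction also links the joint condition to greater susceptibility to fracture, so estimates with and without the injury covariates are best shown side by side.
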